## Abstract

**Background:**

Deprescribing benzodiazepines and related drugs (BZDR) is a challenge due to a lack of time on physicians’ part, a lack of involvement of other health professionals, and the need for adapted tools. This study is based on primary care collaboration, by evaluating the effectiveness of a joint intervention between general practitioners and community pharmacists on the implementation of BZDR deprescribing in older adults.

**Methods:**

This is a cluster randomized controlled trial in which each cluster will be formed by a physician-pharmacist pair. Within a cluster allocated to the intervention, the pharmacist will be trained in motivational interviewing (MI), and will offer the patient 3 interviews after inclusion by the physician. They will base their intervention on validated deprescribing guidelines. The pharmacist will receive methodological support during the first interviews. Interprofessional collaboration will be encouraged by writing reports for the physician after each interview. The following implementation outcomes will be evaluated: acceptability/adoption, appropriateness, cost, and fidelity. They will be measured by means of sociological interviews, observations, logbooks, and cost-utility analysis. Focus groups with physicians and pharmacists will be carried out to identify levers and barriers experienced in this collaboration. Observations will be conducted with pharmacists to assess their approach of the MIs. Effectiveness outcomes will be based on medication (discontinuation or reduction of BZDR) and clinical outcomes (such as quality of life, insomnia or anxiety), assessed by health insurance databases and validated questionnaires.

**Discussion:**

This study will determine whether collaboration in primary care between physicians and pharmacists, as well as training and coaching of pharmacists in motivational interviewing, allows the implementation of BZDR deprescribing in the older adults.

This study will provide an understanding of the processes used to implement deprescribing guidelines, and the contribution of collaborative practice in implementing BZDR discontinuation. The cluster methodology will allow to assess the experience of the relationship between the different primary care actors, and the related obstacles and levers.

The results obtained will make it possible to produce guidelines on the involvement of community pharmacists in the management of substance abuse in older adults, or even to legislate new missions or care pathways.

**Clinical trial registration:**

ClinicalTrials.gov, identifier, NCT05765656.

## Background

According to a 2017 report from the French National Agency for the Safety of Medicines and Health Products (ANSM), 13.4% of the French population used a benzodiazepine or related drug (BZDR) at least once in 2015 (1). These drugs are consumed for hypnotic or anxiolytic purposes in most cases. As per the recommendations, BZDR should not be prescribed for more than 28 days when for hypnotic use and for 8 to 12 weeks, including withdrawal, when for anxiolytic purpose. Indeed, these drugs have shown a real, but mediocre, short-term efficacy on anxiety and sleep disorders (2). Moreover, their long-term effectiveness is almost nil. However, literature shows that nearly one patient out of six taking a BZDR is a long-term user (3) and that the proportion of patients for whom the indication is questionable can reach 2/3 (4). The consequences of BZDR are multiple with an increased risk of daytime sedation, balance disorders leading to falls and fractures, cognitive disorders, road accidents and dementia (1, 2). Also, given their comorbidities, physiological changes, and multiple medications, the older adults are more at risk of experiencing from BZDR adverse events, like falls, driving accidents, dementia or even death (5–9). The majority of patients are unaware of these potential risks and continue to use these medications over the long term. They overestimate the benefits of BZDR and underestimate their harmful effects. The consequences are substantial, both from a health and financial perspective: in France, BZDR represent more than 4% of total drug consumption (10), and 117 million euros in sales (excluding taxes) per year.

At the national level, numerous actions have been taken by the health authorities to reduce the use of BZDR: information for health professionals, pictograms on drug boxes, recommendations by health authorities, incentive measures, and regulatory measures. However, despite these numerous initiatives, the consumption of BZDR remains high. Their deprescribing, defined as discontinuing or reducing under the supervision of a health care professional the dose of medications that are no longer needed, for which risks outweigh the benefits (11, 12) has difficulties being implemented in real life.

Literature shows that many levers can facilitate the implementation of actions for the appropriate use of drugs. Especially, interprofessional collaboration has shown efficacy in improving prescribing appropriateness and affect patients outcomes positively (13–15). As concluded by Nurchis et al., policy makers should promote the widespread adoption of a collaborative approach (15). This may address the discomfort of general practitioners (GPs) who report not feeling fully capable of implementing interventions to deprescribe BZDR if they have to rely solely on guidelines (16), and because of issues such as lack of time to re-assess these treatments, availability of mental health resources, and multiplicity of prescribers (17, 18). Yet, current international deprescribing studies remain mainly based on actions only directed at the prescriber (19), whereas collaboration between primary care professionals appears to be a solution for implementing a decision to stop treatment (17). In addition, BZDR users are very often described as reluctant to stop their medication for fear of a return of anxiety or insomnia (20). In this context, another lever usable to achieve the implementation of deprescribing is the use of techniques that enhance patients’ motivation to change and their engagement in the intervention proposed by their GPs. As such, motivational interviewing (MI) may reduce the extent of substance abuse compared to no intervention (21). Developing and promoting training for healthcare professionals in MI may be a simple and pragmatic implementation strategy to reduce inappropriate BZDR use.

For this study, an interprofessional collaboration between the GP and the pharmacist will be held within primary care setting, with a specific training of pharmacists in MI, allowing the implementation of BZDR deprescribing in the older adults. The acronym BESTOPH-MG stands for “*BEnzodiazépines STOp PHarmacien Médecin Généraliste”(=* “*BEnzodiazepines STOp PHarmacist General Practitioner”).* Clusters composed of a general practitioner and community pharmacist pair will be made and both cluster and patient level objectives will be addressed. The specific aims are (1) to examine implementation outcomes like patient’s factors of receptivity to the intervention, effects of the program on the professional practices of GPs and pharmacists, or reduction in health care consumption, economic efficiency and effectiveness of the intervention on inappropriate BZDR deprescribing rate, and (2) to evaluate if this intervention is associated with improvement in patients reported outcomes and use of other substances following the cessation of BZDR.

## Methods

### Design and setting

This is an open cluster-randomized pragmatic trial with parallel groups and conducted in primary care setting. The study is led by the Nantes University Hospital and is being conducted in the “Pays de la Loire” Region of France. Each cluster will be made up of a GP-Community Pharmacist pair (GP-CP), both of whom already have regular professional exchanges about patients, in order to respect an existing territorial organization. A clustered design was chosen to avoid potential contamination between the intervention and control arms. Indeed, a GP-CP pair applying both the intervention and control condition could lead to patients from the control condition being treated as if they were in the intervention condition. The GP-CP pairs will be randomized with a 1:1 ratio (intervention/control), and all patients handled by the pair will receive the same intervention. If necessary, several physicians from the same practice will be grouped together in the same cluster, and associated with the same pharmacy, in order to be randomized in the same arm and avoid potential contamination between physicians. Figure 1 illustrates the flow chart.

**Figure 1 fig1:**
[figure not shown]
Study flow chart.

### Study population and recruitment

#### Patients

In order to minimize the risk of subjective pre-selection of patients by the GP, a predefined list of eligible patients per cluster will be sent out to each GP by the Health Insurance according to the inclusion criteria detailed below, before randomization of the clusters and on the basis of the GP’s request. The study population will consist of patients aged 65 years and older, monthly users of at least one anxiolytic or hypnotic BZDR for more than 3 consecutive months (ATC classes N05BA, N05CD and N05CF). Patients meeting the eligibility criteria will be recruited by GPs during their medical encounters.

The inclusion criteria will be: outpatients aged 65 and over, followed by the GP and being delivered their medications by the pharmacist of the GP-CP pair, having a prescription for an anxiolytic or hypnotic BZDR prescribed at least 4 times in the past year, the last prescription being dispensed in less than 3 months and having been dispensed monthly during the last 3 months, affiliated to a social security scheme, and having given consent to participate in the research.

Non-inclusion criteria will be: patients living in an institution, participating in another clinical trial, with any medical condition that contraindicates BZDR discontinuation on the physician’s opinion, unable to participate in an interview or answer a questionnaire and with insufficient autonomy to carry out the steps inherent in the study. Patients living in an institution will be excluded because an unknown part of them have their BZDR not traced in the SNDS database (for administrative reasons), which could induce bias in our study.

If eligible, the patient will be offered to enroll in the study during a standard medical consultation. If he agrees to participate, signed informed consent will then be obtained, and the patient will be assigned a patient number automatically upon inclusion.

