#### Primary healthcare professionals

This study will involve GPs and pharmacists practicing in primary care, i.e., in medical practices or community pharmacies. GP and CPs in the Pays de Loire region will be contacted by e-mail through multiple channels like research networks and professional associations. An evening webinar regarding BZDR misuse will be held for physicians and pharmacists in the Region. The objective will be to raise awareness of the problem and to explain the study to professionals. If a GPs shows interest, he/she will be asked to reach out the pharmacist (or vice versa) in order to form a pair (cluster). Pre-existing interactions between healthcare professionals of the same area is a major driver regarding the optimal implementation of the intervention within the cluster. Moreover, as in the context of a pragmatic trial, this way of conducting recruitment is the most coherent regarding the evaluation of what would be observed in practice when deploying the intervention to a larger scale. If both GP and CP agrees to participate, signed informed consent will then be obtained, and the cluster will be randomized.

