### Randomization

A schedule for enrollment, randomization and allocation, interventions, and assessments for the study is presented in Table 1. The randomization will be performed by cluster of GP-CP pairs in open without stratification with a ratio of 1:1 using the *Ennov clinical* software via a secure connection to the servers of the Nantes University Hospital. The information necessary for communication will be provided to the recruiting GPs by a data manager of the Nantes University Hospital. The randomization will be computer-generated by blocks of 6 as the clusters are recruited. The trial statistician and the researchers assessing the outcomes will be blinded to the randomization results.

**Table 1 tab1:** Schedule of enrollment, interventions, and assessments.

	2022	2023			2024		
	June-Dec.	Jan.-Feb.	March-Sept.	Oct.-Dec.	Jan.-March	April–June	July-Sept.
Enrollment							
Recruitment and GP-CP clusters forming	X	X	X				
Eligible patients’ identification			X				
Clusters allocation		X	X				
Intervention							
CP training in MI performing		X	X				
Patients enrollment and MI 1 to 3			X	X			
Monthly reports to GP			X	X	X		
Assessments							
Acceptability/Adoption		X	X				
Appropriateness (interviews)				X		X	
Cost						X	
Fidelity			X	X	X	X	
BZDR consumption				X	X		
Health-outcomes questionnaires				X	X		
Dissemination							X

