#### Step 1: medical encounter with the GP and submission of documents

Patients in the GP-CP clusters randomized to the intervention arm will be offered a joint GP-CP deprescribing intervention by their GP. The physician will present the study schedule to the patients and inform them of the planned follow-ups.

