### Sample size and power

The calculation of the number of subjects needed is based on the effectiveness outcome, on the basis of the following assumptions: risk α equal to 5%, statistical power equal to 80, 5% deprescribing proportion in control group based on current trend, a proportion of at least 15% in the intervention group, an intraclass correlation coefficient of 0.05 (26) and a number of 20 GP-CP pairs per arm. The number of patients to be recruited will be 400 (200 per arm), based on the inclusion of 10 patients per GP-CP pair, with 20 GC-CP pairs per arm during the 12 months of inclusion (27). To reach target sample size, various networks will be involved in recruitment: primary care research network, professional associations, regional unions of practitioners, university training masters.

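### GPs recruit patients after their cluster's arm is known, and Table 1 starts allocation before eligible patients are identified: a risk of differential selection, of unknown direction and size

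*Protocol article*

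**What the plan says.** All references are to the protocol article.

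- **Patients.** The safeguard is introduced with its purpose: "In order to minimize the risk of subjective pre-selection of patients by the GP, a predefined list of eligible patients per cluster" is to be sent by the Health Insurance, at the GP's request and ahead of cluster randomization. The next step is left to the GP: "Patients meeting the eligibility criteria will be recruited by GPs during their medical encounters". Consent is an inclusion criterion. One non-inclusion criterion is a medical condition that, in the physician's opinion, contraindicates stopping the drug.
- **Primary healthcare professionals.** Once GP and pharmacist agree, "signed informed consent will then be obtained, and the cluster will be randomized". The list is not mentioned there.
- **Randomization and Limits.** Allocation is open, and the pairs are not blinded.
- **Step 1.** The offer to patients follows allocation: "Patients in the GP-CP clusters randomized to the intervention arm will be offered a joint GP-CP deprescribing intervention by their GP".
- **Step 2.** Intervention pharmacists are trained in motivational interviewing (MI) beforehand. Control pharmacists are not trained until the study is over.
- **Table 1.** Cluster allocation and pharmacist MI training are both marked for January-February and March-September 2023. Identification of eligible patients is marked for March-September 2023 only.
- **Statistical analysis.** Intention-to-treat covers all included patients. Adjustment covers at least age, sex, past attempts and suspected addiction.
- **Table 3.** Included over eligible patients is a planned acceptability measure.

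**The concern.** In a cluster trial, randomization balances clusters. It balances the patients inside them only if those patients are fixed before allocation is known, or are taken in by a rule that cannot depend on the arm. Here the person who recruits knows the arm, and what the patient is asked to accept differs by arm: three interviews about stopping the drug, or usual care. Both the GP's choice of whom to approach and the patient's decision to consent can therefore differ between arms. Readiness to stop is plausibly related to the primary outcome, since the intervention is built on motivation and ambivalence.

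The plan recognizes the problem and offers the list as the remedy. At stake is whether the list suffices, and whether the schedule lets it exist in time. If not, part of any difference in deprescribing could reflect who was recruited and not what was done for them.

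**Working it through.** **1. Order of events.**

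| Step | Text | Table 1 |
|---|---|---|
| Patient list | before the cluster is randomized (Patients) | identification row: from March 2023 |
| Cluster randomized | after both professionals consent | from January-February 2023 |
| MI training, intervention arm only | before the intervention (Step 2) | from January-February 2023 |
| Patients enrolled | by the GP, after allocation (Step 1) | from March 2023 |

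The training row supports reading the allocation mark as intended. Only intervention pharmacists are trained, so training in January-February requires that some arms be known by then. Any cluster allocated in that period would have its patients identified afterwards. For clusters allocated in March-September the table is too coarse to show a conflict.

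**2. What each safeguard covers.**

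- List: fixes who can be approached, but not who is approached, who is excluded or who consents. The article states no approach-all or ordering rule.
- Intention-to-treat: keeps whoever was included, so it carries any selection forward.
- Named covariates: past attempts and suspected addiction may partly stand in for readiness to stop; motivation itself is not named.
- Blinded statistician and assessors, and the claims-based outcome: protect measurement, not recruitment.
- Included/eligible count: can reveal differential recruitment but does not prevent it.

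**3. The plan's own figure.** Inputs from Sample size and power: "risk α equal to 5"% (two-sided assumed), "statistical power equal to 80"%, "5% deprescribing proportion in control group based on current trend", 15% under intervention, intraclass correlation 0.05, 10 patients per pair, 20 pairs per arm.

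- n per arm without clustering = (0.05×0.95 + 0.15×0.85) × (1.960 + 0.842)² / 0.10² = 137.4
- Design effect = 1 + (10 − 1) × 0.05 = 1.45
- 137.4 × 1.45 = 199.2, so 200 per arm, as stated
- Effective n per arm = 200 / 1.45 = 137.9

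The sample size reproduces, and this point does not affect it.

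**4. Illustration with no true effect.** Every selection input here is assumed.

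*Closed form.* Suppose motivated patients deprescribe at 15% and others at 2.5%, with 20% motivated in the control arm: 0.20×0.15 + 0.80×0.025 = 5.0%. The rejection rate is for a two-sided 5% test of two proportions at effective n 137.9.

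- 30% motivated in the intervention arm: 0.30×0.15 + 0.70×0.025 = 6.25%; rejection 7.3%
- 40% motivated: 0.40×0.15 + 0.60×0.025 = 7.5%; rejection 13.7%
- 10% motivated, if reluctant patients are favoured: 0.10×0.15 + 0.90×0.025 = 3.75%, so the shift runs against the intervention

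*Simulation.* 20 clusters of 10 per arm, intraclass correlation about 0.05, t test on cluster proportions. 30% of listed patients are motivated and deprescribe at 12%, the others at 2%: 0.3×0.12 + 0.7×0.02 = 5.0%. The weight is how many times as readily intervention GPs approach motivated patients.

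| Listed per cluster | Weight 2 | Weight 3 | Weight 5 |
|---|---|---|---|
| 30: intervention-arm rate | 6.2% | 7.0% | 8.0% |
| 30: rejection | 6.6% | 8.9% | 13.9% |
| 15: intervention-arm rate | 5.7% | 6.0% | 6.3% |
| 15: rejection | 5.0% | 6.7% | 6.8% |

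With weight 1 and 30 listed, rejection was 4.7%. Repeat runs at 30 listed gave 5.9% to 6.2%, 8.7% to 9.2% and 13.0% to 13.4% for weights 2, 3 and 5. With 12 listed, rejection stayed near 5%. With both arms favouring motivated patients (weights 3 and 2, 30 listed) it was 5.7%. The 15-patient rows come from 3,000 trials each, so the simulation standard error near 5% is √(0.05×0.95/3000) = 0.4 points.

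**The case against.** The list is a real safeguard: the insurer applies fixed criteria, so GPs do not define the pool. The text places it before randomization in plain words, and that should outrank a coarse schedule. The identification row might mean something other than dispatch of the list. Naming consent as a step before randomization does not say that nothing else precedes it. The covariate set is only a minimum, and Table 3 will count included over eligible patients. The flow chart is not shown, and an article may leave recruitment procedure to the full protocol.

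Most of this narrows the point without removing it. The timing conflict is certain only for January-February allocations, and only if the identification row covers the list. But a contradiction between text and schedule is not omitted detail, and a list that arrives on time still leaves approach and consent open after allocation.

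Four stronger readings are tempting and not supported:

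- *The bias favours the intervention.* The Discussion expects benefit in patients initially reluctant to stop, so intervention GPs might approach them preferentially. The sign is unknown.
- *Type I error is 14%.* That value comes from assumed inputs at the strong end of those tried. The document gives no list size and nothing on selection strength.
- *GPs may exclude whomever they wish.* The criterion requires a contraindicating medical condition; the opinion concerns that condition.
- *Fixed blocks make allocation predictable.* The article says "The randomization will be computer-generated by blocks of 6 as the clusters are recruited", but exploiting this needs knowledge of earlier allocations and control over which pair comes next. Nothing shows that anyone has both.

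**Conclusion.** The point holds as a design risk with an internal contradiction attached. Patients are recruited by GPs who know the arm, and the list controls only the candidate pool. For clusters allocated in January-February 2023, Table 1 as written removes the timing on which that safeguard depends.

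The consequence is possible differential selection of patients between arms, in either direction. The document shows no realized imbalance and gives no basis for estimating one. In the scenarios above type I error runs from about 5% to 14%. It is near nominal when the list is barely longer than the number recruited, and higher when the list is long and one arm selects strongly. The range is illustrative and not a bound. The calculations also leave out the planned covariate adjustment, which could absorb part of a shift. The change is worth making because it is cheap and acts where the bias could enter; analysis of included patients alone cannot reliably undo it later.

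**What to change.** 1. State that no cluster is randomized until its Health Insurance list has been received and frozen, and repeat this where professional consent triggers randomization.
2. Correct Table 1 to match, so that identification of eligible patients precedes allocation, and hence MI training, for every cluster.
3. Instruct GPs in both arms to approach every listed patient as they attend, or to follow a random order set in advance.
4. Log listed patients as approached, excluded (with reason), refused or included, and report these counts by arm. This extends the included/eligible measure already in Table 3.

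Optionally, add a sensitivity analysis of the claims-based outcome (SNDS) in all listed patients. It would include people who did not consent, so it is possible only if data permissions and consent rules allow.

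The cost is a recruitment instruction, a short log and a corrected table. The downside is slightly less GP freedom and possibly slower inclusion. Approaching listed patients as they attend fits recruitment at ordinary consultations better than a strict random order. The sample size does not change.
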